## Abstract

**Introduction:** Previous studies have shown an improvement in the access to treatment for patients with first-episode psychosis (FEP), specifically young patients, through mobile app–based interventions. The aim of this study is to test the effectiveness of a mobile app–based intervention to improve community functioning in adolescents with FEP. Mobile app–based interventions could increase quality of life and disease awareness, which improve adherence to treatment and reduce the frequency of relapses and rehospitalizations in adolescents with FEP.

**Methods:** This article describes a mobile app treatment and the pilot trial protocol for patients with FEP. We will perform a single-blind randomized clinical trial (RCT) including patients with FEP aged 14–19 years recruited from Gregorio Marañón Hospital, Madrid, Spain. Patients will be randomly assigned to an intervention group, which will receive treatment as usual plus five modules of a psychological intervention through the mobile app (psychoeducation, recognition of symptoms and prevention of relapses, problem solving, mindfulness, and contact wall), or to a control group (standard care). The effectiveness of the intervention will be assessed by means of an extensive battery of clinical tests at baseline and at 3 months of follow-up. The primary outcome is reduction in psychotic and depressive symptoms; secondary outcomes comprise adherence, awareness, use of drugs, and quality of life. Data will be analyzed on an intention-to-treat (ITT) basis. Mixed model repeated-measures analysis will be used to explore the following effect: group × time interaction between the control group and the intervention group for clinical and functional variables during the follow-up period.

**Discussion:** This is an innovative study for the assessment of a psychological intervention through a mobile app for patients with FEP during the critical period. This pilot RCT is intended to be a precursor to larger studies, which in turn could facilitate dissemination of mobile app therapy for patients with FEP.

**Ethics and Dissemination:** The local ethics committee approved the study protocol. All participants must sign the informed consent, to participate. After finalizing the study, the results will be published.

**Trial registration:** NCT03161249. NCT clinicaltrials.gov. Date of registration in primary registry 02 May 2017. clinicaltrials.gov.

## Introduction

Psychotic disorders typically emerge in adolescence and young adulthood. While some patients recover fully, many experience persistent difficulties, or remain vulnerable to future episodes. The course of psychotic disorders with onset in childhood or adolescence is variable, although overall prognosis is usually worse than for adults (1, 2). Moreover, adolescence is a critical period for biological, psychological, and social development. Consequently, the emergence of a severe psychiatric disorder at this stage could have a strong impact on personal achievements and cause major disability (3). Five years after the onset of first-episode psychosis (FEP), the relapse rate reaches 70–80% (4); therefore, early intervention is a priority. Psychological intervention may significantly improve symptomatology, functional recovery, prognosis, and quality of life in FEP patients (5). Available approaches usually take the form of assertive outreach programs (e.g., cognitive behavior therapy, medication, family support), which include a combination of psychoeducational interventions aimed at family groups (6–8). However, some studies show that the benefits of these kinds of interventions are not maintained in the long term (9–12). In this context, online interventions could be a therapeutic complement to maintain the effectiveness of psychosocial interventions that have already shown their effectiveness in the short and medium term (13).

With the rise of new technologies, research on psychological interventions during adolescence has incorporated the use of various electronic applications, social networks, and other similar tools to provide new methods/routes of communication between therapists and patients. This new therapeutic approach may provide patients with personalized, flexible, and evidence-based interventions in their communities and even in their own homes (14).

Although the use of technological advances in psychiatric treatment is relatively recent, the availability and sophistication of technologies are growing. This is particularly true for smartphones and mobile applications, which are one of the most rapidly expanding and adopted forms of technology in history (15). Available research suggests that in western countries, up to 90% of people diagnosed with FEP have access to a smartphone (16, 17).

Some studies have reported results for smartphone-based interventions and conclude they are feasible, attractive, and safe in young patients with FEP or psychosis (18–20), although it must be stressed that adherence depends on these factors (19). Thus, most patients perceive this type of intervention to be positive and useful and show adequate adherence to the intervention during follow-up (21). With respect to specific diagnoses, a recent study shows the feasibility, acceptability, and preliminary efficacy of such interventions for patients with schizophrenia (22). In terms of symptoms, studies report improvements in affective and psychotic symptoms, number of admissions, sociability, and adherence to treatment (20, 21, 23). Nevertheless, despite the fact that some studies report that these on-line interventions are feasible and safe in young patients, more randomized controlled clinical trials are needed to consistently assess the effectiveness of digital interventions in FEP (24).

The aim of this study is to test the effectiveness of a mobile app–based intervention to improve community functioning in adolescents with FEP. It may also increase quality of life and disease awareness, which will lead to greater adherence to treatment and fewer relapses and rehospitalizations.

To our knowledge, this is the first clinical study to evaluate the effectiveness of an online intervention through a mobile app specifically designed for adolescents with FEP, as a complement to their usual treatment. We hypothesized that participants in the app group would find the online intervention acceptable, useable, attractive, and helpful. We also hypothesized that participants' in the app group would experience fewer psychotic and affective symptoms and that global functioning and adherence to treatment and quality of life would be better than in the treatment as usual group. We provide a detailed description of the study design, patient selection and evaluation, and the psychological treatment modules under study (implemented by a mobile app).

## Aims

The aim of this study is to evaluate the efficacy of an online intervention focused on symptoms (psychotics and depressive) compared to a treatment as usual in adolescent patients with early psychosis on several variables including adherence, awareness, prognosis, use of drugs, and quality of life.

## Methods and Analysis

### Design

We designed a pilot randomized controlled trial (RCT) of a smartphone application used in conjunction with usual care and compared it with usual care alone in adolescents with FEP. The trial is to be performed single-blind and at a single center.

### Patients' Recruitment

We will recruit patients from the Child and Adolescent Psychiatry Department of Hospital General Universitario Gregorio Marañón in Madrid, Spain between 2018 and 2019. Recruitment will begin after the protocol has been published. Patients who agree to participate in the study will be assessed and randomly assigned to the intervention group (mobile app intervention) or to the control group (standard care). The intervention group will receive treatment as usual plus a psychological intervention through a mobile app. The control group will receive only the treatment as usual (pharmacotherapy together with regular sessions with a psychiatrist and/or clinical psychologist). The pharmacological treatment will be that prescribed by the patient's psychiatrist.

#### Patients' Inclusion Criteria

The inclusion criterion for patients will be age 14–19 years with the presence of at least one positive psychotic symptom (delusions or hallucinations) before age 19 years and 1 of the following diagnoses from DSM-5 (25): schizophrenia, schizoaffective disorder, schizophreniform disorder, bipolar disorder, major depressive disorder with psychotic features, brief psychotic disorder, or psychosis not otherwise specified. They must also be fluent in Spanish and give their written informed consent to participate. In the case of minors, parents or legal guardians will be required to provide their written informed consent prior to inclusion. The patient must also agree to participate. Furthermore, all patients will have to have spent at least 2 months free from hallucinatory or delusional psychotic symptoms.

#### Patients' Exclusion Criteria

*Exclusion criteria*: Patients with intellectual disability, organic brain disorders, comorbid conditions that could hinder communication, or drug abuse as a primary diagnosis will be excluded.

### Randomization and Blinding

Patients will be randomized to the groups (1:1) using the program “random allocation software.” The person in charge of the assessments will not be involved in the treatment program and will be blind to this process. Study evaluators will be blind to the treatment branch and trained not to comment on it. In emergency cases, the patient will be excluded from the study. This situation will be indicated in the protocol, although the patient will continue with his/her usual treatment and be treated by his/her reference psychiatrist, who will be informed of this situation and ensure that appropriate clinical treatment is administered.

The flow diagram of the study can be seen in Figure 1.

**Figure 1 F1:**
[figure not shown]
Participant flow diagram.

### Ethical Criteria and Ethics Committee

The project will be conducted according to local regulations and the internationally established principles of the Declaration of Helsinki (Fortaleza, Brazil, 2013). The study and the protocol were approved by the Clinical Research Ethics Committee of each participating health center (UNIR University and Gregorio Marañón Hospital: Certificate no. 06/2017). Written informed consent will be required for all participants, in the case of minors, parents or legal guardians will be required added to provide their written informed consent prior to inclusion.

### Sample Size Calculation

Few previous longitudinal studies have analyzed children and adolescents with the characteristics of the patients in the present study (26, 27). Sample size was calculated based on data published in the literature related to the main issue addressed in the study (28), namely, mu1 (42.5) and mu2 (31.9), sigma value (11.54), value for α (0.05), and value for desired power (0.80). The proposed sample size was 50 patients-−25 per group—which is anticipated to be further reduced by loss to follow-up, resulting in an approximate final sample of 38–42 patients. In order to obtain a power of 80% to detect differences from the null hypothesis, H0: μ1 = μ2, using inferences to compare the means of two independent samples, with a significance level of 5%, we need to include at least 19 patients in the experimental group and 19 patients in the control group. Recruitment of participants is adjusted to 25 per group to account for possible dropouts.

### Clinical Assessment Criteria

Data on the major clinical and demographic variables will be entered on a data collection form. All patients will be assessed by blind raters at baseline and at 3 months after inclusion in the study, after signature of informed consent, and randomization. During follow-up, patients who use the app will be “monitored” by mental health professionals. Their reference clinicians will fully informed, and families will know that the adolescents are participating in the study. Any emergency or major side effect in either of the study arms will be pointed out, and the patient will be removed from the study. If necessary, the patient will be referred to the emergency department.

All the instruments used in the study have appropriate psychometric properties (29–31).

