## Statistical Analysis

Data will be analyzed on an intention-to-treat (ITT) basis (68). In accordance with the ITT principle, all patients will be included in the analysis, independently of the groups to which they are randomly assigned and regardless of whether they complete the treatment or not.

Outcomes will be reported with 95% confidence intervals. All data will be analyzed using SPSS version 21.0. The level of bilateral significance for all statistical tests will be established at α = 0.05.

The baseline characteristics of the sample will be compared between the two groups using the Pearson chi square test for the categorical variables and the *t* test or Mann-Whitney test for the quantitative variables.

Mixed model repeated-measures analysis will be used to explore the following effects: group × time interaction between the control group and the intervention group for clinical and functional variables during the follow-up period. Intergroup and intragroup differences during follow-up will also be studied.

The effect sizes will be calculated to quantify the effect of the intervention on the groups. To consider a certain value a large or small effect size, the following orientations will be accepted: *d* = 0.20 (small), *d* = 0.50 (moderate), and *d* = 0.80 (large) (69).

The research results will be reported in agreement with the Consolidated Standards of Reporting Trials (CONSORT) 2010 statements (70, 71) and the Standard Protocol Item: Recommendations for Interventional Trials (SPIRIT) guidelines (72, 73).

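### Randomised patients with an emergency or major side effect leave the study, with no stated 3-month assessment, although the analysis is to be intention-to-treat on all patients

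*Protocol article*

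**What the plan says.** Three sections of the protocol article bear on this point.

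- **Clinical Assessment Criteria**: any emergency or major side effect, in either arm, "will be pointed out, and the patient will be removed from the study". The same section sets the blinded assessments for all patients at baseline and at 3 months.
- **Randomization and Blinding**: "In emergency cases, the patient will be excluded from the study". It adds that "the patient will continue with his/her usual treatment and be treated by his/her reference psychiatrist". Usual care is described, but no further study assessment.
- **Statistical Analysis**: "Data will be analyzed on an intention-to-treat (ITT) basis". It continues: "In accordance with the ITT principle, all patients will be included in the analysis", and this holds "regardless of whether they complete the treatment or not". The method is a repeated-measures mixed model, and the effect of interest is the group × time interaction.

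**The concern.** The removal rule acts after randomisation and is triggered by a clinical event. The primary outcome in the Abstract is reduction in psychotic and depressive symptoms. An emergency in this population could well be a worsening of those symptoms, in which case the rule stops data collection for a reason linked to the outcome.

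The loss may also differ by arm. Only app patients are monitored by professionals during follow-up (Clinical Assessment Criteria) and complete weekly symptom checks that can advise them to see a clinician (Module on Recognition of Symptoms and Prevention of Relapses). The app is also expected to reduce relapses and rehospitalisations (Introduction). Better detection would raise removals in the app arm, and real benefit would lower them.

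At stake is whether the estimate describes everyone randomised or only those who had no crisis. A 3-month score that was never collected cannot be recovered by any later analysis plan.

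**Working it through.** **Does removal mean only stopping the app?** No. The rule covers either arm, and control patients have no app to stop. For them it can only mean leaving the study.

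**What does a removed patient contribute?** There are two time points, baseline and 3 months. A patient removed before 3 months has at most the baseline score. If baseline is modelled as a response, the patient can formally stay in the mixed model, but with almost no information on change by group. The model then relies on the missing score being predictable from baseline, which is doubtful if the emergency was itself a worsening of symptoms.

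**The plan's own sample size** (Sample Size Calculation: means 42.5 and 31.9, SD 11.54, two-sided α 0.05, power 0.80)

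- Difference = 42.5 − 31.9 = 10.6; d = 10.6 / 11.54 = 0.92.
- n per group = 2 × (1.960 + 0.842)² / 0.9185² = 18.6, rounded up to 19. This reproduces the stated 19.
- Recruiting 25 per group leaves a margin of 6 per arm. A final 38–42 of 50 is a loss of 16–24%.

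Keeping emergency cases under follow-up does not change this requirement.

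**How many patients?** The documents give no emergency rate. As a proxy, take the five-year relapse rate of 70–80% (Introduction) at constant hazard:

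- 3-month risk = 1 − (1 − r)^(3/60).
- r = 0.70: 1 − 0.30^0.05 = 5.8%; × 50 = 2.9 patients.
- r = 0.80: 1 − 0.20^0.05 = 7.7%; × 50 = 3.9 patients.

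Relapse is not the same as emergency. Entry also requires at least 2 months free of hallucinations and delusions, so the true 3-month rate could be higher or lower.

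**How much bias?** Let c control and a app patients be removed out of 25 per arm, each scoring k SD worse than those remaining in the same arm. The full-sample difference exceeds the difference among those remaining by (c − a)/25 × k SD. The splits and k are assumptions.

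| Removed (control / app) | k = 1 | k = 2 | k = 3 |
|---|---|---|---|
| 2 / 2 | 0 | 0 | 0 |
| 2 / 1 | 0.04 | 0.08 | 0.12 |
| 3 / 1 | 0.08 | 0.16 | 0.24 |
| 1 / 2 | −0.04 | −0.08 | −0.12 |

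Positive values are benefit hidden; negative values flatter the app. Against 0.92 SD, the 3/1 row is 0.08/0.92 = 9% to 0.24/0.92 = 26%.

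**A second illustration** assumes normal scores (higher is worse) and removal of exactly the worst scorers, which is a strong assumption.

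- True difference 10.6, one severity threshold for both arms: if 5%, 10%, 16% or 24% of controls exceed it, the difference among those remaining is 9.5, 8.8, 8.0 or 7.2, an attenuation of 10%, 17%, 24% or 32%.
- True difference zero, worst 4% removed from one arm and 12% from the other (1 and 3 of 25): a spurious 1.6 points, or 1.6/11.54 = 0.14 SD, favouring the arm with more removals.

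**The case against.** The strongest reply is that the sections are not strictly incompatible. A mixed model can keep a removed patient through the baseline score, and the handling of missing scores is commonly left to an analysis plan that is not shown. That stands as far as it goes: a reader might infer that the two rules can never both be followed, and the text does not prove this. But keeping a patient nominally in the model supplies no outcome, and an analysis plan can only handle scores as missing if the protocol stops their collection.

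Three other strong readings are tempting but not supported.

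- *The rule deletes the worst outcomes from both arms.* The document does not define an emergency, and a major side effect may have nothing to do with symptom scores. That emergencies are often relapses is plausible but is an assumption.
- *The safety record is suppressed.* Both sections say the event is flagged, and the reference psychiatrist is to be informed. What is lost is information after the event.
- *About a quarter of the planned effect is erased.* That is one corner of the table. Equal removals with equal severity give zero, and other splits reverse the sign.

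It is also fair to say that this is a pilot of 50 patients that already allows for 16–24% loss. The allowance protects the numbers, not against bias from who is lost.

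**Conclusion.** The concern holds in this form: the removal rule and the intention-to-treat statement need reconciling, because following the rule as written loses 3-month scores for reasons plausibly tied to the primary outcome. On the relapse proxy, 3–4 of 50 patients would be affected. The bias runs from nil to about 0.08–0.24 SD for a 3-versus-1 split, against a planned 0.92 SD, and its direction is unknown. These sizes rest on the proxy rate, the constant hazard, the assumed split and the assumed severity; the contradiction in the text rests on none of them.

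A lesser wording fault sits beside it. Statistical Analysis says "all patients will be included in the analysis, independently of the groups to which they are randomly assigned", whereas intention-to-treat analyses patients in the group to which they were assigned. Since the same section tests group × time by arm, this is probably a drafting slip and adds no weight to the main point.

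**What to change.** Reconcile Randomization and Blinding, Clinical Assessment Criteria and Statistical Analysis. The clinical response to an emergency, and any stopping of the app, stay as they are; the change concerns outcome data only. State that:

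1. patients with an emergency or major side effect remain under outcome follow-up;
2. the 3-month assessment is sought if they still consent;
3. they are analysed in the group to which they were randomised, with the sentence on assigned groups corrected to match.

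A sensitivity analysis that gives an unfavourable value to emergency patients without a 3-month score is optional, and is one choice among several.

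The cost is a change of wording and a few 3-month assessments of patients who would otherwise have left the study (about 3–4 on the proxy rate). The required sample size does not change.

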#### Demographic Data

Age, sex, level of education, living arrangements, and employment or educational status will be collected from each participant. All diagnoses will be made by the patient's reference psychiatrist, and assessments will be conducted blind by psychiatrists/psychologists experienced in child and adolescent psychiatric disorders.

#### Evaluation of Patients' Symptoms

Psychotic symptoms will be assessed using the Positive and Negative Syndrome Scale PANSS (32), which is composed of 30 items covering positive and negative symptoms and the general psychopathology of the disorder. Each item is measured using a 7-point Likert scale reflecting the severity of symptoms from 1 (none) to 7 (extreme symptoms). The scale has been validated for the Spanish population (33). In addition, Positive symptoms will be assessed using SAPS (34) and negative symptoms using SANS (35), both of which were validated in Spanish by Vazquez in 1989 (36, 37). SAPS has 34 items and SANS 25. Both have good psychometric properties.

Trait and state anxiety will be measured using the State-Trait Anxiety Inventory (STAI) (38). This instrument has two parts: one that assesses the anxiety experienced by patients during the previous week (namely “state”) using 20 items with 4 response options; and another that assesses their usual reactions to specific situations (namely “trait anxiety”), also using 20 items with 4 response options. The STAI was adapted from the Spanish study in 1978 by Bermudez (39), who found that in these items, the mean and the reliability (Cronbach alpha and test-retest correlation) were similar to those of the original version (40).

Mood symptoms will be evaluated using the Hamilton Rating Scale for Depression (HRSD) (41) validated for the Spanish population (42). This instrument is in three different versions (5, 7, 21 items) and has good psychometric properties. The 21-item version will be used for this study.

